## Abstract

**Background:**

Buttabean Motivation (BBM) is a Pacific-led organisation which aims to reduce obesity amongst Pacific and Māori people in New Zealand enabling them to choose a healthy and active life-style for the duration of their lives, their children, their wider family and the community. BBM offers a holistic approach to weight loss, recognising that mental health, family and cultural factors all play essential and critical role in nutrition and physical activity patterns. This study aims to evaluate the effectiveness of BBM for sustained health and wellbeing outcomes among its predominantly Pacific and Māori participants for both general BBM members and those with morbid obesity attending the ‘From the Couch’ programme.

**Methods:**

Quasi-experimental pre-post quantitative cohort study design with measured or self-reported weight at various time intervals for both cohorts. Weight will be analysed with general linear mixed model for repeated measures, and compared with a prediction model generated from the literature using a mixed method meta-analysis. The secondary outcome is change in pre- and post scores of Māori scale of health and well-being, Hua Oranga.

**Discussion:**

Multiple studies have shown that many diet and physical activity programmes can create short-term weight loss. The fundamental question is whether BBM members maintain weight loss over time. In New Zealand, Pacific and Māori engagement in health enhancing programmes remains an important strategy for achieving better health and wellbeing outcomes, and quality of life. Internationally, the collectivist cultures of indigenous and migrant and minority populations, living within dominant individualist western ideologies, have much greater burdens of obesity. If BBM members demonstrate sustained weight loss, this culturally informed community-based approach could benefit to other indigenous and migrant populations.

**Trial registration:**

Australian New Zealand Clinical Trial Registry ACTRN12621000931875 (BBM general members) First submitted 10 May 2021, registration completed 15 July 2021. ACTRN12621001676808 7 (From the Couch) First submitted 28 October 2021, registration completed 7 December 2021.

## Background

Obesity now presents the biggest health risk in Pacific populations in New Zealand. This is well documented and widely accepted. Yet despite community and government efforts to promote weight loss and encourage engagement in lifestyle change programmes, Pacific and Māori continue to have far higher rates in obesity and weight-related diseases in Aotearoa New Zealand compared with their non-Pacific, non-Māori counterparts [1]. As little as 5% weight loss for a person with obesity can lead to clinically significant reductions in several weight-related comorbidities [2]. The flow-on benefits of sustained weight loss on other risk factors such as hypertension, and hyperlipidaemia, incidence and management of diseases such as diabetes and sleep apnoea, and even mortality are well established. Too often after initial weight loss success, weight increases return and chronic illnesses persist due to shortcomings of intervention programmes, such as their short-term nature, design or costs involved, in addition to the ongoing ease of passive over-consumption in an obesogenic food environment [3]. Most existing evaluations of weight loss programmes are researcher-initiated, engage predominantly at an individual level and use stringent research designs, particularly randomised control trials. Biomedically-based interventions are often delivered by ‘experts’ to individuals or small groups without community leadership and input, and programme life expectancies can end up matching the duration of research grants.

The challenge of creating an effective programme by and for indigenous and migrant communities that successfully achieves ongoing engagement and results in sustained weight loss is still to be met [4]. A culturally-centred, community wrap-around approach is needed to inspire a sense of commitment and sustained motivation.

Buttabean Motivation (BBM) is a major Pacific-led organisation of promise that has emerged within this environment. BBM originates from the professional pseudonym ‘Brown Buttabean’ used by former boxer and founder of BBM, [name]. At first glance, BBM is another physical activity programme aimed at addressing ‘the alarming obesity statistics among Māori and Pasifika’ in Aotearoa New Zealand. However, BBM offers a more holistic community-based approach, recognising that cultural factors play an essential and critical role in determining community nutrition and physical activity patterns. Physical activity is important for reducing risk of obesity, cardiovascular disease, stroke, and several other chronic diseases including type 2 diabetes, hypertension, and it impacts positively on psychological disorders (depression, anxiety), and overall quality of life [5]. Crucially, physical exercise offers a viable entry point for Pasifika and Māori on the path to wellbeing, with fitness, strength and dance being highly resonant with cultural values and practice. In the context of an obesogenic environment, sociocultural factors (norms, values and beliefs) are important in understanding and mitigating adverse social determinants on health [6].

BBM transcends conventional western definitions and parameters of weight loss programmes, emphasising a Pacific-centric philosophy in relation to family and community, rather than, highlighting individual aims in achieving personal health or a desired body aesthetic. Pacific and Māori cultural values and beliefs are demonstrated in the programme’s wider social support initiatives, such as pop-up health clinics and community education, finding innovative ways to motivate participants to adopt wider lifestyle actions around diet and other health behaviours. This philosophy is also visible in more fundamental forms of social support offered, such as community housing and a food bank, which are well-established factors influencing nutrition-related health outcomes. Very few existing weight loss programmes employ a holistic community focussed approach. Despite the challenges of evaluating evolving, holistic programmes, especially with the disruptions caused by Covid-19 impacts on people’s lives and social interactions, it is important to answer research questions of effectiveness and impact of such community-led programmes [7].

BBM was set up in 2014 and, by September 2021, there were over 15,000 members who variably participated in several programmes including 34 weekly free community bootcamps. BBM also offers a 12-week ‘From the Couch’ (FTC) programme, which is a highly supportive, holistic, physical activity and tailored diet programme designed for individuals who are usually morbidly obese and have very restricted physical capacity, such as not being able to ‘get off the couch or who struggle to stand for very long periods of time’. The FTC programme aims to enable individuals to move ‘from the couch’ towards eventually being able to do everyday activities, which most able-bodied people take for granted.

The BBM programme warrants a full evaluation not only to measure its social and health impacts, but to understand its internal dynamics, values and strengths to inform continuous programme improvement and increase reach and effectiveness [8]. A preliminary qualitative study using the Fonofale Pacific framework of inquiry [9] has explored the lived experience of Pacific and Māori clients and trainers. A further study is underway to conduct a process evaluation of BBM’s community engagement through its in-person, social and news media outreach activities with respect to the health and wellbeing of Pasifika and Māori people in their community over time. The underlying sociocultural values that determine sustained motivation, engagement and impact, and how these are associated with biomedical outcomes needed to be researched.

### Aim and objectives

The aim of this study is to evaluate the effectiveness of BBM for sustained health and wellbeing outcomes among its predominantly Pacific and Māori participants. The primary hypothesis is that BBM will create valuable, average sustained weight loss (≥ 5% of baseline weight) for participants over three years. Secondary hypotheses include that programme participation will result in improved quality of life (measured in Hua Oranga); and for the FTC cohort, improved cardiovascular and metabolic health outcomes (measured via medical records).

There are two research questions. The first is, how effective are BBM’s general programmes in providing sustained weight loss of ≥ 5% of baseline body weight and improved quality of life measures for its members? The objective is to carry out an impact assessment of BBM’s general programme effectiveness, to estimate the medium to long-term (one to two year) weight loss maintenance and the impact on quality of life of BBM members.

The second question is how effective is BBM’s FTC programme for achieving sustained clinically significant benefits for members who typically experience of Class 3 or 4 obesity [10]? The objective here is an outcome assessment of the FTC programme’s effectiveness, to examine the medium to long-term clinical impact on a sub-cohort (n ~ 50) of members who enter BBM with Class 3 and 4 obesity, body mass index (BMI) > 35 kg/m^2^. As secondary outcomes, we will collect laboratory and clinical data from medical records held by primary care providers. Data collection will occur on three occasions, at commencement of the FTC programme, one and two years later.

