### Variables

For the general programme group, enrolment measurements will be height in metres and weight in kilograms (kg), and they will complete a Māori scale of health and well-being, Hua oranga, electronically. Their weight in kg will be recorded at six and 12 months, and at conclusion at 24 months, they will repeat Hua oranga and have a final weight taken. The primary outcome will be changes in weight, and the secondary outcome will be changes in Hua oranga scores. Note that first measurement is at enrolment in the evaluation and many participants at this stage will have been in the BBM programme for a period of time already. At enrolment, their self-reported heaviest weight, and weight at their first BBM visit will be recorded.

For the FTC group, in addition to the data collected above, clinical data from their health records will be sought. This includes diagnosis classifications, past history and current problems of any chronic diseases, especially type 2 diabetes, hypertension, gout, dyslipidaemia, cardiovascular disease, stroke, renal dysfunction, liver disease, osteoarthritis, gall bladder disease, chronic obstructive respiratory disease, and obstructive sleep apnoea. Blood and urine analyses laboratory results, prescribed medications, and other referral letters and discharge summaries will also be accessed. Their blood pressure at enrolment and at 12-weeks will also be recorded.

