### Statistical analysis

All statistical analysis will be done in R [13] using the lme4 package [14]. The primary outcome of interest is sustained weight loss. How successful BBM is at helping participants lose and maintain 5% weight loss will be a critical outcome measure, however, the effectiveness of BBM compared to other counterfactuals will also be assessed.

The general programme cohort will include existing and new entrants. For existing members we will also have self-reported weights at their first BBM session, which will be considered the baseline or ‘time zero (T0)’ weight with subsequent times measured from then. For example, for a person who started at BBM seven months before enrolment in the study, their reported weight at BBM entry will be T0, their enrolment weight (measured by the research team at study enrolment) will be T7, their 6-month weight will be T13, 24-month weight will be T31. Typically, the pattern of weight loss with weight loss programmes is tick-shaped with a weight loss nadir at 6–12 months followed slow return back towards T0 weight or beyond. Estimated duration of the study will be 24 months of follow-up from enrolment.

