### Determination of the counterfactuals for comparison

Since there is no enrolled comparison group in this study, the counterfactuals to be included to determine how effective BBM is will be threefold:Versus similar New Zealand population. The estimated mean weight change of ethnic/gender/age groups will be derived from the last five years of NZ Health Surveys [15] and these will be compared with the general programme groups participating in BBM. Note that, longitudinally, weight change in a subpopulation is the additive effects of secular changes to weight (ie each age group gets a little heavier each year) and age-related weight change (ie the person moves to an older age group which has a higher average weight).Versus control groups in other similar studies. A literature review [16] has identified five weight loss studies with predominantly Pacific or Māori participants that had control groups (total *N* = 955, follow-up 3–24 months) [17–21]. Their weight change trajectories will be compared to the BBM general programme participants.Versus other interventions. The literature review noted above [16] identified 18 studies with various interventions with weight change outcomes [17–34]. These combined results show how effective other programmes have been. Since the duration of interventions varies (3–24 months), weight loss is not linear.

A mixed method meta-analysis was conducted using the metaphor package [35] in R. Studies were only included in this analysis where the difference with baseline (time 0) was published together with their standard error, standard deviation, or confidence interval (to enable calculation of the standard error). Figure 1 shows the forest plot of the included studies.

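### The primary hypothesis is set at three years, but follow-up ends 24 months after enrolment; only members with at least 12 months' prior membership can reach three years, from a self-reported baseline

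*Protocol article*

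**What the plan says.** Aim and objectives in the protocol article puts the primary hypothesis as an average sustained loss of at least 5% "of baseline weight) for participants over three years". The next paragraph gives the general-programme objective as "to estimate the medium to long-term (one to two year) weight loss maintenance". For the FTC cohort's medical records, the same section says "Data collection will occur on three occasions, at commencement of the FTC programme, one and two years later".

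The measurement schedule follows the shorter horizon. Variables says that general members, "at conclusion at 24 months, they will repeat Hua oranga and have a final weight taken". Statistical analysis says "Estimated duration of the study will be 24 months of follow-up from enrolment". Participant recruitment foresees a one-year extension because of COVID-19, but its stated purpose is to complete the 24-month follow-up. It adds no later visit.

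Statistical analysis also sets the clock. For existing members, the self-reported weight at the first BBM session is the T0 "weight with subsequent times measured from then". In its example, a member who joined seven months before enrolment has a "24-month weight will be T31".

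For the external comparison, Determination of the counterfactuals for comparison describes the five studies with control groups as "total *N* = 955, follow-up 3–24 months". It gives the same 3 to 24 months as the range of intervention durations. The fitted spline has one knot, at two months. Study data are to be compared with this curve by t-probabilities at time points that are not named.

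**The concern.** The hypothesis, the objective and the visit schedule do not share a horizon. Sustained loss is the primary outcome, and the Discussion calls long-term maintenance the fundamental question, so the horizon is part of the primary claim.

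If it is left open, success could be declared at 24 months in everyone or at three years in long-standing members only, and the choice could be made after the results are seen. A three-year figure would come from people who stayed. The Discussion itself says that length of engagement is closely tied to maintenance of weight loss, so that subgroup is selected on a correlate of the outcome.

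A second, separate issue concerns the literature curve. Existing members' final weights fall after T24, where the studies behind the curve, as described, have no data. A t-test there would treat an extrapolated comparator as if it had been observed.

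**Working it through.** **Inputs**
- Hypothesis horizon: 36 months (Aim and objectives).
- Objective horizon: 12 to 24 months (same section).
- Weights after enrolment: 0, 6, 12 and 24 months (Variables).
- Time origin for existing members: first BBM session (Statistical analysis).
- Literature range: 3 to 24 months, as follow-up for the control studies and as duration for the interventions.
- Start of BBM: 2014 (Background). Study setting: from 2021.

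**Formula.** Let p be months in BBM before enrolment. Time of a weight = p + months since enrolment, so the last observed time = p + 24.

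**The article's own example.** With p = 7: 7 + 0 = 7, 7 + 6 = 13, 7 + 12 = 19, 7 + 24 = 31. This reproduces its T7, T13 and T31.

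**Who reaches T36?** p + 24 ≥ 36 requires p ≥ 36 − 24 = 12 months.

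| Prior membership p (months) | Last time | Against T36 | Months beyond T24 |
|---|---|---|---|
| 0 (new entrant, or FTC followed from entry) | T24 | 12 short | 0 |
| 7 (the article's example) | T31 | 5 short | 7 |
| 11 | T35 | 1 short | 11 |
| 12 | T36 | reached | 12 |
| 24 | T48 | passed | 24 |

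The extreme case is a 2014 joiner enrolled in 2021: p is about 84, so the last time is about 84 + 24 = T108. This is an upper bound, not a typical member.

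**Share reaching T36.** Variables says that many participants will already be in BBM at enrolment, but gives no number and no distribution of p. The share with p ≥ 12 could be anywhere from 0% to 100% of existing members.

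**The curve.** Every member with p > 0 has a final weight p months past the stated literature limit. With the only knot at two months, any prediction beyond T24 extends the segment that begins there. The article describes the later part of the fitted shape as weight regain. If that rise were carried past 24 months, the comparator would keep regaining with no data behind it, which would favour BBM. Fig. 2 is not available here, so this direction is conditional.

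**The case against.** A reader might infer that the three-year hypothesis cannot be tested at all. The documents do not support that. Under the T0 rule, anyone with at least 12 months' prior membership contributes a weight at T36 or later, and many participants are expected to be existing members. What remains is narrower: such data come from a selected subgroup with a self-reported baseline, while the hypothesis speaks of participants generally.

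A reader might also infer that the range of the literature curve limits the primary test. It does not. The 5% criterion is judged against the participant's own baseline, and the curve serves only the counterfactual comparison. That comparison has other arms not tied to 24 months: the national health survey and, in the Discussion, the assumption of no weight change.

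Nor does the article commit itself to late curve comparisons. It names no comparison points, T31 only illustrates the time scale, and the choice may sit in an analysis plan not shown. For the intervention studies, 3 to 24 months is given as duration rather than follow-up, so the plotted range cannot be confirmed. All of this stands, and it makes the extrapolation a risk to close off rather than a stated error.

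Finally, it can be said that one phrase is out of step with an otherwise consistent 24-month plan. That is fair, but the phrase sits in the primary hypothesis.

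**Conclusion.** The point holds in two parts of unequal weight.

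First, the three-year horizon contradicts the one-to-two-year objective and the 24-month schedule. The gap is 12 months for new entrants and for FTC participants followed from entry, and 5 months for the article's own example member. Three-year data exist only for p ≥ 12 months, in still-attending members with a self-reported T0. A three-year claim for participants in general is therefore not supported. This rests on the stated visit times alone.

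Second, comparisons with the literature curve after T24 would be extrapolation, by 7 months at T31. This assumes that the stated 3 to 24 months is the range of the data behind the curve and that late comparison points would be used. Comparisons up to T24 are not affected.

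**What to change.** - Restate the primary hypothesis as average loss of at least 5% at 24 months, in line with the objective and the schedule.
- Keep the T0 definition in Statistical analysis. Report new entrants (T0 at enrolment) separately from existing members (self-reported T0). Replacing T0 with the measured enrolment weight for everyone would not be a repair: an existing member who had lost 8% before enrolment and kept it off would count as 0% loss.
- Present any estimate at T36 or later as secondary and descriptive, restricted to members with at least 12 months' prior membership and labelled as such.
- Limit t-tests against the literature curve to times at or before 24 months from T0.

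No visits or measurements are added. The cost is wording in the hypothesis and analysis sections, a less ambitious claim, and a registry update if the three-year horizon is recorded there.

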## Methods/design

### Study design

This is a quasi-experimental quantitative cohort study design. The general programmes participants will have pre-measurements (measured or self-reported weight at entry to BBM) and multiple post-measurements (measured weight at various intervals), and the FTC participants will have pre-post programme weight measurements. Evidence from the literature of the natural course of weight change in populations like the BBM participants with and without interventions will enable counterfactual comparisons. This study follows the Strengthening the Reporting of Observational Studies in Epidemiology (STROBE) Statement and a Standard Protocol Items: Recommendations for Intervention Trials (SPIRIT) checklist has been completed.

### Setting

Attendees of BBM programmes in Auckland from 2021.

### Participant recruitment

For the general programme, participants will be recruited through study advertisements on BBM’s social media platforms, and as posters in physical locations (the exercise centres). BBM trainers will promote the study to BBM attendees. All attendees over the age of 16 years will be eligible to participate.

For FTC group participants, all people registering for three 12-week programmes will be invited to enrol in the study. All FTC participants will be eligible, with the exclusion of repeat attenders already enrolled in the study.

Participants from both the general and FTC groups will be offered a koha (gift) of a $40 token at the 24-month follow-up. Participants will continue to be enrolled until the target samples are reached. Given recurrent lockdowns and restrictions on class sizes due to COVID-19, it is anticipated that the study will be extended by one year to enable 24 month follow-up of all participants.

### Sample size calculations

The study has a finite population and has a quasi-experimental design of an existing intervention with no randomised sample, hence our sample size needs to take a pragmatic approach. We will recruit a many eligible participants as possible in the available timeFor the general group the target is to recruit 1000 BBM members, and for FTC. there are about 20 enrolees in each FTC programme, and some repeat the cycle, so the total number is estimated to be about 50 over three cycles.

